## Abstract

*Background*: Parkinson’s disease (PD) is the second most common neurodegenerative disorder. This disease is characterized by motor symptoms, such as bradykinesia, tremor, and rigidity. Although balance impairment is characteristic of advanced stages, it can be present with less intensity since the beginning of the disease. Approximately 60% of PD patients fall once a year and 40% recurrently. On the other hand, cognitive symptoms affect up to 20% of patients with PD in early stages and can even precede the onset of motor symptoms. There are cognitive requirements for balance and can be challenged when attention is diverted or reduced, linking a worse balance and a higher probability of falls with a slower cognitive processing speed and attentional problems. Cognitive rehabilitation of attention and processing speed can lead to an improvement in postural stability in patients with Parkinson’s. *Methods*: We present a parallel and controlled randomized clinical trial (RCT) to assess the impact on balance of a protocol based on cognitive rehabilitation focused on sustained attention through the NeuronUP platform (Neuronup SI, La Rioja, Spain) in patients with PD. For 4 weeks, patients in the experimental group will receive cognitive therapy three days a week while the control group will not receive any therapy. The protocol has been registered at trials.gov NCT04730466. *Conclusions*: Cognitive therapy efficacy on balance improvement may open the possibility of new rehabilitation strategies for prevention of falls in PD, reducing morbidity, and saving costs to the health care system.

## 1. Introduction

Parkinson’s disease (PD) is the second most common neurodegenerative disorder. This disease is characterized by motor symptoms, such as bradykinesia, tremor, and rigidity. Non-motor symptoms such as cognitive impairment, anosmia, sleep disorders, or depression are also part of the disease, and although their prevalence is very high, they are often underdiagnosed [1,2].

One of the cognitive characteristics in PD is the slowness in the processing of information, which includes deficits in processing speed and attention, cognitive inflexibility, and forgetfulness [3]. These symptoms may appear from the initial stages of the disease [4].

Approximately 60% of PD patients fall once a year and 40% do so regularly [5]. These falls may be correlated with the inability to achieve compensatory movements to regain balance when their center of gravity generally oscillates outside their limits of stability (LOS), which is reduced in this disease [6]. Some authors point out that reaction times and processing speed [7] may be a marker of postural instability since a reduced speed is associated with difficulty in making turns [8]. This is in line with Pantall’s findings, indicating that cognitive function and postural control progressively worsen with disease progression [9].

The relationship between cognitive impairment and postural instability in PD patients may be specific for tasks that assess the dorsolateral prefrontal cortex and its frontal–subcortical connections [10]. The main cognitive functions whose affectation would influence a worse balance and gait performance would be attention and executive functions [7,11,12,13]. Varalta et al. [12] specified that balance is related to executive functions and attention, while functional mobility is related to cognitive impairment, verbal fluency, and attentional capacity.

Some authors point out that within the executive functions the component with the greatest weight in this relationship would be the inhibitory control [13]. Dual-task performance has also been established as a good indicator of falls in patients with early-stage PD and no previous history of falls [14]. The studies that carried out a one and a half years follow-up of the participants concluded that the deterioration of executive functions acts as a predictor of future falls in patients with PD [7,9,15,16].

Cognitive rehabilitation through neurorehabilitation platforms and neuropsychological rehabilitation in patients with Parkinson’s disease has shown to be effective in improving processing speed, attention, and executive functions [17,18,19,20].

Although the relationship between cognitive deficits and postural stability seems to be demonstrated [21] we have not found studies that, through cognitive rehabilitation, seek a stability improvement.

The main aim of this study is to conduct a parallel and controlled randomized clinical trial to validate a rehabilitation protocol for sustained attention and information processing speed in patients with Parkinson’s disease, targeting changes in 1. instrumental and clinical evaluation of postural stability and 2. wide neuropsychological and neurophysiological evaluation. Our main hypothesis is that the group that receives cognitive rehabilitation will improve their postural stability compared to the group that does not undergo any therapy. If this hypothesis is confirmed it will open the possibility of new rehabilitation strategies for prevention of falls in PD, reducing morbidity, and saving costs to the health care system.

## 2. Materials and Methods

Mat the Standard Protocol Items: Recommended Items for Interventional Trials (SPIRIT) 2013 checklist has been used to assure the quality of the protocol [22].

### 2.1. Study Design and Participants

The participants will be recruited in PD outpatient’s clinic of the Beata María Ana Hospital of Madrid and referred from other collaborators centers and hospitals or self-referrals that know the research project due to the dissemination through social networks. The subjects included will be assessed by a neurologist expert in movement disorders ([name])) (Figure 1). All patients will be idiopathic PD patients diagnosed according to the UK Parkinson’s Disease Society Brain Bank criteria. The inclusion and exclusion criteria are shown in Table 1. During the protocol, changes in dopaminergic medication will be prohibited and, if necessary, will lead to the exclusion of the patient. The total daily dose of dopaminergic drugs will be recorded and controlled in the final analysis of the results.

To control the Wearing-off effect, a specific questionnaire will be applied both at the beginning and at the end of the study [23].

The data will be anonymized and will be recorded separately, being safeguarded in accordance with current European data protection laws. All data will be recorded and verified twice in a database designed for the study.

The study design will be a parallel, randomized and controlled experimental study. The patients included in the sample will be divided into two groups: Cognitive rehabilitation (experimental) and no therapy (control). The distribution will be random, but it will be ensured that there is an equitable number of subjects in each of the stages of the disease, being matched by their score in HY. The randomization of the sample will be done through the website: http://www.randomization.com/ (accessed on 12 February 2020). The duration of the study will be 18 months.

The sample will be composed of 46 patients randomly distributed in a 1:1 ratio (Figure 1). To calculate the sample size, we used the GRANMO calculator. Accepting an alpha risk of 0.05 and a beta risk of 0.2 in a one-sided contrast, 23 subjects are required to detect a difference equal to 12 points in the Biodex objective stability limits test assessment (Biodex, Version 1.08, Biodex, Inc., Shirley, NY, USA). The standard deviation in the stability limits test obtained in our sample from the NeuroMOD project was 16.16. Considering a 15% loss, it will be necessary to reach a sample of 26 patients in each group.

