### 2.2. Intervention Protocol

The intervention sessions will be held at the patient’s home. If this is not possible, they will be carried out in the research laboratory of the Beata María Ana Hospital or in the Parkinson’s patients association or current attending hospital of the patient.

Depending on the assignment to each of the experimental groups, the patients will undergo neurorehabilitation of cognitive functions or will not receive any therapy.

Due to the characteristics of the study, all participants will know the experimental group to which they belong. The researcher evaluating the preintervention and postintervention balance is blinded to the experimental group.

Control Group: The control group will not receive any therapy. They will be simply evaluated at the same time as the experimental group.

Experimental Group: In the experimental group, patients will receive a 12-session neuropsychological rehabilitation protocol that will be carried out over four weeks (3 weekly sessions). The protocol and the number of sessions has been designed by neuropsychologists following the Díez-Cirarda et al. recommendations [24] (Figure 1 and Figure 2).

Each session will consist of a series of cognitive stimulation tasks aimed at improving attention, perception, and processing speed. These tasks will be applied through the NeuronUp (Neuronup SI, La Rioja, Spain) cognitive neurorehabilitation platform to achieve maximum homogeneity and objectivity in their application. The protocol is preprogrammed in the application and is identical for all patients. Performing tasks through the platform allows one to objectively record the performance of each patient in all tasks to ensure adherence and efficacy. Before the first session, a training session will be carried out under the supervision of a researcher. All doubts that may arise will be resolved.

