### 2.4. Data Analyses

The SPSS software package (version 25.00; SPSS Inc., Chicago, IL, USA; IBM, New York, NY, USA) will be used by a blinded statistician for statistical analysis of the data. Demographic and clinical variables will be presented as mean and standard deviation. A 95% confidence interval (CI) will be taken, considering statistically significant all those values that had a *p* < 0.05. Parametric statistical tests will be used for hypothesis testing (*n* > 30). To show the differences in the variables, a 2 × 2 analysis of variance (ANOVA) of repeated measures will be carried out, taking time and group as factors, being the control and experimental groups and the pretreatment and posttreatment time measures. If significant differences are found in any of the interactions, a post hoc analysis with Bonferroni correction will be performed. The effect sizes will be calculated using Cohen’s d, classifying them into small (d between 0.20 and 0.49), medium (d between 0.50 and 0.79), or large (d greater than 0.80) following Cohen’s method.

Possible confounders or mediating variables will be included as covariates in the analysis.

For the rest of the variables, a Pearson correlation or linear regression will be carried out with the motor and balance variables. The low correlation will be that with values between 0.2 and 0.39; the correlation will be considered moderate when the value goes from 0.40 to 0.79; and high when the correlation value is greater than 0.80.

For the EEG entropy analysis, nonparametric Kruskal–Wallis (KW) tests will be performed to compare the distributions, the Mann–Whitney U test to evaluate the difference between the median values, and the Wilcoxon rank sum test for measure pre/post intervention changes, with a significance level of 0.05 and the alternative hypothesis of unequal values. Therefore, small *p*-values will suggest significant differences between populations.

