## 3. Discussion

The main objective of the study is to improve the balance of Parkinson’s patients through cognitive rehabilitation. Cognitive rehabilitation in PD has been effective in the rehabilitation of attention and executive functions [44], on the other hand, previous studies relate attention and executive functions with the risk of falls, balance, and gait in PD patients, proposing rehabilitation in these areas as a possible effective therapy [8,45].

All the clinical variables assessed will allow one to identify markers that predict a better outcome of the cognitive intervention on balance rehabilitation, this information will be of great relevance to adjust the intervention to specific profiles of patients with PD who will benefit the most.

Although our study counts with the limitation of a lack of blinding of the participants and some researchers, its design is robust enough to provide with evidence that may support new approaches to stability rehabilitation in PD. Current strategies continue to be based on training in compensatory and signaling strategies, high intensity visual rehabilitation, and exercise such as dance, Tai-Chi, and Yoga [46]. Other studies use virtual reality as part of therapy although there is still no evidence on its efficacy [47]. The use of virtual reality implies the transfer of patients to a specialized center and continuous supervision. Our study proposes a home-based protocol that can improve the quality of life of Parkinson’s patients even from their own home avoiding the current pandemic limitations on medical care.

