**Figure 2 medicina-57-00314-f002:**
[figure not shown]
Schematic representation of the study experimental procedures.

**Table 1 medicina-57-00314-t001:** Inclusion and exclusion criteria.

Inclusion Criteria	Exclusion Criteria
Idiopathic Parkinson’s disease (diagnosed according to the UK Parkinson’s Disease Society Brain Bank criteria). Older than 18. Stage < III Hoehn–Yahr with no obvious motor fluctuations.	Visual-perceptual difficulties. Peripheral sensory disturbances due to polyneuropathy. Cerebellar alterations. Impossibility to operate a computer due to motor impairment Severe cognitive impairment (MoCA < 24). Moderate or severe active depression (BDI > 14). Dependence (mRS > 3). Dopaminergic medication changes in the last 30 days. Structural changes MRI Severe comorbidity (cancer, severe COPD, etc.). Atypical data for idiopathic PD.

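### Excluding randomised patients who need a dopaminergic medication change can bias the comparison of arms in either direction, by an amount the protocol does not allow one to compute

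*Protocol article*

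**What the plan says.** Section 2.1 of the protocol article sets the rule that, during the protocol, "changes in dopaminergic medication will be prohibited and, if necessary, will lead to the exclusion of the patient". It then adds one analysis provision on medication: "The total daily dose of dopaminergic drugs will be recorded and controlled in the final analysis of the results".

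Table 1 lists a different medication rule among the exclusion criteria for entry: "Dopaminergic medication changes in the last 30 days".

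On blinding, section 2.2 says that "all participants will know the experimental group to which they belong", and also that "The researcher evaluating the preintervention and postintervention balance is blinded to the experimental group". Section 2.4 says that the software "will be used by a blinded statistician for statistical analysis of the data". The Discussion names as a limitation the "lack of blinding of the participants and some researchers".

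Section 2.2 also gives the two arms different amounts of contact. In the experimental arm a researcher keeps in touch with the patient, gives reminders, checks that each session was done, and evaluates adverse effects after sessions, with a physician informed if they persist. Controls receive no therapy and are only assessed at the same time points.

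**The concern.** Randomisation makes the arms comparable at entry. That protection covers the final comparison only if patients are not removed because of something that happens afterwards. A need to change dopaminergic medication is such an event. It plausibly reflects the patient's motor state, and the protocol itself treats dopaminergic state as relevant to its measurements: assessments are made in the ON state, UPDRS III is recorded beforehand, and wearing-off is checked by questionnaire.

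If these events arise, or come to light, at different rates or for different reasons in the two arms, the remaining patients are no longer a fully randomised comparison. In a trial with 23 to 26 patients per arm, 10% of one arm is only two or three patients (0.10 × 23 = 2.3; 0.10 × 26 = 2.6), so a handful of informative losses can move the estimate. What is at stake is the validity of the main balance comparison.

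**Working it through.** **Step 1. Does the rule reach randomised patients?** The Table 1 criterion looks back 30 days and governs entry. The section 2.1 sentence governs changes while the protocol is running and stands apart from that criterion. Its plain reading therefore covers patients already allocated.

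**Step 2. Does the meaning of exclusion matter?** The article does not say whether the patient leaves the study, the analysis, or both. If the study, the post-intervention assessment is not made. If the analysis, a randomised patient is dropped because of a post-baseline event. Either way the patient is lost from the comparison.

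**Step 3. Do the other provisions repair this?** Blinded balance assessment protects how patients are scored, not who remains to be scored. A blinded statistician cannot analyse an absent outcome. Adjustment for daily dose works only on patients still in the data.

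**Step 4. The plan's own figures.** Inputs from section 2.1: difference 12, SD 16.16, one-sided alpha 0.05, power 0.80.

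n per arm = 2 × [16.16 × (1.645 + 0.842) / 12]² = 22.4, rounded up to 23, which agrees with the article. For 15% loss the article gives 26 per group. Here 22.4 / 0.85 = 26.4 and 23 / 0.85 = 27.1, so the stated figure is close. The effect size and SD are taken as stated.

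**Step 5. Illustration of size.** The exclusion rates and correlations are assumptions; the article gives none. Suppose there is no treatment effect, scores are normal with SD 16.16, and a fraction p is excluded from one arm only, with correlation r between the exclusion tendency and a poor score. The mean of those remaining shifts by

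shift = r × SD × φ(z_p) / (1 − p).

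- p = 0.05, r = 1: 16.16 × 0.1031 / 0.95 = 1.75 points, or 1.75 / 12 = 15% of the target difference.
- p = 0.10, r = 1: 16.16 × 0.1755 / 0.90 = 3.15 points, or 3.15 / 12 = 26%.

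| Excluded, one arm only | r = 1 (exactly the worst scorers) | r = 0.5 | r = 0.3 |
|---|---|---|---|
| 5% | 1.75 | 0.88 | 0.53 |
| 10% | 3.15 | 1.58 | 0.95 |
| 15% | 4.43 | 2.22 | 1.33 |

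At 5% to 10% and r of 0.3 to 0.5, the shift is thus about 0.5 to 1.6 points (4% to 13% of 12). The last row places the whole 15% loss allowance in one arm. If 15% are excluded in one arm and 5% in the other at r = 0.5, the net shift is 2.22 − 0.88 = 1.34. If the rates and r are equal in both arms, the shifts cancel. The sign depends on which arm loses patients and on whether they are its poor or good performers.

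**Step 6. Effect on false positives.** A simulation under the same assumptions (100,000 trials per setting, 23 or 26 per arm, two-sample t-test, two-sided 5% level, no true effect) gave these error rates:

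- 15% lost from one arm: about 0.06 at r = 0.3, 0.07 to 0.08 at r = 0.5, and 0.15 to 0.16 at r = 1.
- 15% against 5% at r = 0.5: about 0.06.
- Equal exclusion of 15% in both arms at r = 0.5: about 0.05.

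**Step 7. What this does not measure.** Section 2.4 plans a 2 × 2 time-by-group analysis, so the treatment contrast rests on pre-to-post change. Excluding patients who score poorly at both visits leaves that contrast unmoved; only exclusion related to change shifts it. The article gives no SD of change, so steps 5 and 6 describe the score and do not predict the bias in the planned contrast.

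**The case against.** The case on the other side has real force on size.

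- **Events may be few.** The intervention lasts four weeks, patients are below Hoehn–Yahr stage III without obvious motor fluctuations, and medication has been stable for 30 days at entry. This stands.
- **The prohibition is identical in both arms, and nothing shows that seated computer tasks alter the need for medication.** This also stands. The argument for unequal removal is indirect: participants know their allocation, and the experimental arm is contacted and questioned far more often, so a need may come to light more readily there. That makes imbalance possible; it does not document it.
- **The 1.8 and 3.2 point shifts are extreme.** They require every exclusion to fall in one arm and to be exactly its worst scorers, so a reader should not take them as expected bias. At more moderate assumed correlations the shift is smaller, and with balanced, equally outcome-related exclusions it is about zero.
- **The full protocol or an analysis plan may define analysis sets.** The article's silence on an intention-to-treat set is therefore not a fault, and none is alleged. The point rests on the exclusion sentence, which is a stated rule. If the rule ends follow-up, no later analysis plan can recover an assessment that was never made.
- **Calling the trial open-label would overstate matters.** The lack of blinding described concerns participants and some researchers; the balance assessor and the statistician are blinded. That protects measurement and analysis but does not prevent selective removal.

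**Conclusion.** The point holds as a risk that should be removed. The article fixes a rule that takes randomised patients out of the comparison because of a post-randomisation event plausibly related to balance, and no other stated provision brings them back.

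Its size and direction are unknown. The illustrative figures rest on assumed exclusion rates, assumed correlations, normal scores and exclusions confined to one arm: up to 1.8 or 3.2 points at 5% or 10% exclusion of exactly the worst scorers, and about 0.5 to 1.6 points at correlations of 0.3 to 0.5.

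A reader might infer that the rule will favour cognitive rehabilitation, or that the trial's result will be invalid. The document supports neither. The bias could run either way, could be negligible over four weeks in this population, and is about zero if exclusions are balanced and equally related to outcome. The change is worth making because it is cheap and removes a source of bias that cannot be corrected after the data are lost.

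**What to change.** Leave the clinical rule on medication, and on whether the intervention continues, to the investigators. Change only what the rule does to the data:

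1. State that a patient whose medication changes is, with the patient's agreement, still assessed at the scheduled post-intervention visit.
2. Record the date of the change and the change in total daily dopaminergic dose.
3. Include the patient in the primary analysis in the arm to which he or she was randomised.
4. Make the analysis that leaves out patients with a medication change a sensitivity analysis, and report the number of such patients by arm.

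The cost is some protocol wording and keeping an already planned assessment for what is probably a small number of patients. The drawback is that the primary estimate will include a few patients whose medication was altered; the sensitivity analysis shows how much that matters. Patients who decline the post-intervention visit will still be missing, so the change reduces the problem without guaranteeing complete data.

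### The sample size rests on a one-sided 0.05 test, but the analysis section plans a non-directional ANOVA at p < 0.05 with a 95% CI; on the sizing inputs, power at 23 per arm is about 69%, not 80%

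*Protocol article*

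**What the plan says.** Section 2.1 (Study Design and Participants) gives the sizing: "Accepting an alpha risk of 0.05 and a beta risk of 0.2 in a one-sided contrast, 23 subjects are required". The target is a 12-point difference on the Biodex stability limits test. The variability comes from an earlier project: "The standard deviation in the stability limits test obtained in our sample from the NeuroMOD project was 16.16". The article does not say whether this is the SD of a single score or of a change.

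Two enrolment figures follow in the same section: "The sample will be composed of 46 patients randomly distributed in a 1:1 ratio", and then "Considering a 15% loss, it will be necessary to reach a sample of 26 patients in each group".

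Section 2.4 (Data Analyses) sets the decision rule: "A 95% confidence interval (CI) will be taken, considering statistically significant all those values that had a *p* < 0.05". The method is "a 2 × 2 analysis of variance (ANOVA) of repeated measures will be carried out, taking time and group as factors". For the balance outcomes it states no one-sided contrast, halved p-value, 90% interval or one-sided bound. The main hypothesis in the Introduction is directional: it expects improvement with rehabilitation relative to no therapy.

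**The concern.** A sample size is valid for the test it was computed for. Here the sizing test puts the whole 5% in one tail. With two groups and two time points, the time-by-group F statistic is the square of the t statistic on change scores, so its 5% is split over both directions. A 95% interval likewise matches a two-sided 0.05 test. The planned analysis therefore has a higher threshold than the one that produced 23 per arm.

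Two things are at stake. First, a null result on balance would be read as coming from a trial with 80% power when, on the sizing inputs, it has less. Second, an unresolved convention leaves a choice open after the results are known: a two-sided p between 0.05 and 0.10 in the hoped-for direction could be called significant by pointing to the sizing paragraph.

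**Working it through.** **Inputs** (section 2.1): difference δ = 12; SD σ = 16.16; α = 0.05; power 80%; 23 per arm; 15% loss; 46 in total or 26 per arm. From section 2.4: p < 0.05, 95% CI, 2 × 2 repeated-measures ANOVA.

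**Step 1. Reproduce the stated 23.** Two-sample normal formula: n per arm = 2(z_α + z_0.80)²(σ/δ)², with (16.16/12)² = 1.8135.

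- One-sided: 2 × (1.645 + 0.842)² × 1.8135 = 22.42, so 23. This is the stated figure.
- Two-sided: 2 × (1.960 + 0.842)² × 1.8135 = 28.47, so 29. The noncentral t gives 30.
- A one-sample or paired formula gives 12 (one-sided) or 15 (two-sided).
- The one-sided noncentral t gives 24.

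Of these, only the one-sided two-sample normal formula gives 23, so 23 is a per-arm number and depends on the one-sided choice.

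**Step 2. Power of the planned test on the same inputs.** This takes 16.16 as the SD of whatever is compared. At 23 per arm the standard error is 16.16 × √(2/23) = 4.765 and δ/SE = 12/4.765 = 2.518.

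- Normal, two-sided: Φ(2.518 − 1.960) = 71.2%.
- Noncentral t, 44 df, two-sided: 69.3%.
- For comparison, one-sided: 80.9% (normal), 79.8% (t).

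The other sample sizes that the article implies, two-sided:

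| Evaluable per arm | How it arises | Power (t) | Power (normal) |
|---|---|---|---|
| 19 to 20 | 46 enrolled, 15% lost (23 × 0.85 = 19.55) | 60.5% to 62.9% | 62.9% to 65.1% |
| 22 | 26 per arm enrolled, 15% lost (26 × 0.85 = 22.1) | 67.2% | 69.3% |
| 23 | no loss from 46 | 69.3% | 71.2% |
| 26 | no loss from 52 | 74.7% | 76.3% |

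None reaches 80%.

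**Step 3. Detectable difference at 23 per arm, two-sided, 80% power.** Normal: (1.960 + 0.842) × 4.765 = 13.4 points. Noncentral t: 13.7 points.

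**Step 4. If 16.16 is a single-score SD.** The time-by-group test then works on changes with SD = 16.16 × √(2(1 − ρ)), where ρ is the pre/post correlation, assuming equal pre and post SDs. The article gives no ρ, so the values below are assumptions. Two-sided t power at 23 per arm:

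| ρ | SD of change | Power |
|---|---|---|
| 0 | 22.85 | 41% |
| 0.25 | 19.79 | 52% |
| 0.5 | 16.16 | 69% |
| 0.6 | 14.45 | 79% |
| 0.7 | 12.52 | 89% |

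The 69% in step 2 is thus the case where 16.16 is the change SD or, equivalently, a single-score SD with ρ = 0.5.

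**The case against.** The strongest reply is that the hypothesis is directional and the time-by-group test has one degree of freedom, so a signed, one-sided t test can be taken from the same model. The article never calls the ANOVA two-sided. That is fair: a one-sided design is legitimate if carried through, and the two-sided reading is an inference from the F test, the 95% interval and the unqualified p < 0.05. But section 2.4 does not carry the direction through. The only alternative hypothesis it spells out, for the EEG tests, is one of inequality.

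A second reply is that repeated measures may have more power than a plain two-group comparison. They may, and step 4 shows they may also have less. The sizing paragraph invokes no correlation, so it cannot be credited with one.

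A reader might infer that the trial's true power is 69% or lower. The article does not support that. The 69% depends on what the SD refers to; full retention of 26 per arm gives about 75%; and with a single-score SD, a correlation of 0.7 gives 89%. A reader might also infer that the sample size was miscalculated on its own terms. It was not: 23 per arm reproduces exactly for the one-sided test.

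Nor is this a detail that an article can leave to a fuller document. Both statements are printed here, and they do not agree.

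**Conclusion.** The concern stands as an inconsistency between sections 2.1 and 2.4. The stated 80% belongs to a one-sided test that the analysis section does not plan. On the sizing inputs, the type II error at 23 per arm is about 31% (1 − 0.693) rather than the 20% claimed, and no enrolment figure in the article restores 80%. This rests on two assumptions: that the ANOVA is read two-sided, as its decision rule implies, and that 16.16 is the SD of the quantity compared. If the second fails, power is undetermined without the pre/post correlation, and the stated 80% is then unsupported rather than shown to be too high. That 46 in total does not agree with 26 per group is a separate matter; both readings are shown above so that the conclusion does not depend on it.

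**What to change.** Settle one convention before the data are analysed.

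- **Two-sided.** Keep p < 0.05 and the 95% CI, delete the one-sided wording in section 2.1, and state whether 16.16 is a single-score or a change SD. Then restate the power (about 69% at 23 evaluable per arm on the sizing inputs) or the detectable difference (13.7 points by t, 13.4 by the normal approximation). Restoring 80% for 12 points would instead take 29 to 30 evaluable per arm, which is 35 to 36 enrolled per arm at 15% loss (29/0.85 = 34.1; 30/0.85 = 35.3).
- **One-sided.** Keep the sizing, and name the primary test in section 2.4 as a one-sided time-by-group (change-score) contrast, reported with a matching one-sided bound. The group main effect is not the right contrast, because it averages the pre and post measurements and dilutes an effect that appears only afterwards.

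Baseline-adjusted ANCOVA is an optional way to recover power, but only with its assumption stated. If 16.16 is a single-score SD and the correlation is 0.5, the residual SD is 16.16 × √(1 − 0.25) = 13.99 and two-sided power at 23 per arm is about 81%.

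Unless more patients are recruited, the change is to wording only. Under the two-sided option, its cost is a less favourable stated power.

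### The article gives two unreconciled sample sizes, 46 in total and 26 per group (52); if 46 is the number randomised, it has no allowance for the assumed 15% loss and one-sided power is about 74–75%, not 80%

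*Protocol article*

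**What the plan says.** All the relevant statements stand in one paragraph of the protocol article, section 2.1 (Study Design and Participants).

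- Planned sample: "The sample will be composed of 46 patients randomly distributed in a 1:1 ratio".
- Error rates: "Accepting an alpha risk of 0.05 and a beta risk of 0.2 in a one-sided contrast".
- Result of the calculation: "23 subjects are required to detect a difference equal to 12 points" on the Biodex stability limits test.
- Variability: "The standard deviation in the stability limits test obtained in our sample from the NeuroMOD project was 16.16".
- Allowance for loss: "Considering a 15% loss, it will be necessary to reach a sample of 26 patients in each group".

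The first statement means 23 per arm and the last means 26 per arm, or 52 in total. No sentence connects them.

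**The concern.** The randomisation target decides how long the allocation list is, when recruitment ends, and what the final report is checked against. Here a team that stopped at 46 and a team that went on to 52 could each point to a sentence in the same paragraph.

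The two figures also differ in substance. Forty-six looks like the bare calculated number doubled, with nothing added for the loss that the paragraph itself assumes. Some loss is built into the design, because section 2.1 removes any patient whose dopaminergic medication has to change during the study. If 46 is what will be randomised, the analysis set would be smaller than the calculation requires, and the chance of missing the 12-point difference would be higher than the stated 0.2.

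**Working it through.** **Inputs, all from section 2.1:** difference δ = 12; SD σ = 16.16; one-sided α = 0.05 (z = 1.645); β = 0.2 (z = 0.842); 1:1 allocation; loss 15%.

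**1. Reproduce the stated 23.** For two independent means,

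n per arm = 2 × (z₁₋α + z₁₋β)² × (σ/δ)² = 2 × 6.1826 × 1.8135 = 22.42, rounded up to 23.

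This matches the article exactly. A two-sided test would give 28.47, so 29 per arm, and a one-sided paired calculation 11.2, so 12. The 23 is therefore the one-sided, two-group number **per arm, before loss**.

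**2. Where 46 comes from.** 2 × 23 = 46. It contains no allowance for loss.

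**3. Where 26 comes from.** The article does not say. Marking up the unrounded number gives 22.42 × 1.15 = 25.8, which rounds to 26. Dividing instead gives 22.42/0.85 = 26.4. From the rounded 23, the results are 23 × 1.15 = 26.45 and 23/0.85 = 27.06. So 26 is reachable from the unrounded figure by a simple mark-up.

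**4. Power under each reading.** Normal approximation: power = Φ(δ / (σ√(2/n)) − 1.645). The t column uses the noncentral t distribution with 2n − 2 degrees of freedom.

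| Randomised | Evaluable after 15% loss | Per arm | Power, normal | Power, t |
|---|---|---|---|---|
| 46 | 46 × 0.85 = 39.1 | 19.55 | 75.1% | 73.7% |
| 52 | 52 × 0.85 = 44.2 | 22.1 | 79.5% | 78.3% |
| reference: 23 per arm evaluable | 46 | 23 | 80.9% | 79.8% |

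For 46 randomised, the normal formula reads 12 / (16.16 × √(2/19.55)) = 12/5.169 = 2.322; 2.322 − 1.645 = 0.677; Φ(0.677) = 0.751.

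**5. Size of the gap.** At 46 randomised, power is about 5 to 6 points below 80%, so β is about 0.25–0.26 instead of 0.20. At 52 randomised, it is 0.5 points below 80% by the normal method, which is the one that reproduces the 23, and 1.7 points below by t.

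**6. Minor note on rounding.** To leave 23 evaluable per arm, 23/0.85 = 27.06, so strictly 28 per arm (56 in total). Twenty-seven per arm would leave 27 × 0.85 = 22.95.

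**The case against.** **The two numbers may mean different things.** Since 46 is 2 × 23, it could be the evaluable target, with 52 the number to recruit. The closing sentence of the paragraph fits that reading. Against it, the article ties 46 to random allocation, which makes it the randomised number on its face. The paragraph refers to Figure 1 at that point, and the figure is not shown, so it may settle the matter. What stands is that the power loss is conditional on 46 being the number randomised; the text still needs correcting either way.

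**A reader might infer that neither figure delivers the stated power,** because 26 × 0.85 = 22.1 is below 23. The inequality is true, but the inference is not supported. The unrounded requirement is 22.42, so 22.1 falls about 0.3 of a patient short per arm. By t, even 23 evaluable per arm gives 79.8%, so a strict 80% line would fail the article's own number too. At 52 the shortfall is at rounding level.

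**A reader might also take 74–75% as the power of the planned analysis.** The documents do not support that either. Section 2.4 plans a 2 × 2 repeated-measures ANOVA with covariates, and its power for the group-by-time effect depends on the pre–post correlation, which is not given. Nor does section 2.1 say whether 16.16 is the SD of a score or of a change. If it is a score SD, one-sided t power for the comparison of changes at 19.55 per arm would be 61%, 74% or 90% at assumed correlations of 0.3, 0.5 or 0.7. The uncertainty runs both ways. The figures above measure departure from the protocol's own sizing calculation and nothing more.

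**Conclusion.** The point holds as an internal contradiction with a conditional loss of power. The article states two sample sizes, 46 and 52, and does not reconcile them. Because both are stated, this is not a detail that a condensed article has left to a fuller document. If 46 is randomised, the assumed 15% loss leaves about 39 evaluable patients and one-sided power of about 74–75% against the stated 80%. If 52 is randomised, about 44 are evaluable and power is about 78–79.5%, which is near enough to the claim.

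These results assume loss spread evenly over the arms, an unadjusted one-sided comparison of two means, and the article's own difference and SD. The difference between 26 and 28 per arm is a minor note and would not by itself call for a change.

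**What to change.** State one randomisation target in section 2.1, with its arithmetic, and bring Figure 1 into line if it differs. Two ways to do this:

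- **52 randomised (26 per arm).** State about 44 evaluable after 15% loss and one-sided power of about 79%. Either delete 46 or label it as the evaluable number that the calculation requires before loss. It should not be presented as the expected evaluable number: keeping 46 of 52 would need a loss of no more than 6/52 = 11.5%.
- **46 randomised (23 per arm).** State about 39 evaluable after 15% loss and one-sided power of about 74–75%, and delete the 26 per group.

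If the sponsor wants 23 evaluable per arm strictly, the number to randomise is 28 per arm (56 in total).

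The cost is one corrected paragraph and no new procedure. Keeping 46 means publishing a less favourable power. Choosing 52 means recruiting 6 more patients than the opening sentence implies, and 56 means 10 more.
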